### Recruitment {15}

The subjects will be recruited from the inpatients in the Infectious Department of the Third Affiliated Hospital of Sun Yat-Sen University. Recruitment is expected to begin in August 2021 and end in December 2023.

## Assignment of interventions: allocation

### Sequence generation {16a}

After inclusion in the trial, the randomization adopts a simple randomization method, and random numbers are generated through computer software (SAS9.4) by the statistician.

### Concealment mechanism {16b}

The method of allocation concealment is envelope concealment. Random numbers will be put into uniform envelopes. Then, subjects will be given uniform envelopes according to the order of inclusion and will be assigned random numbers in the envelopes.

### Implementation {16c}

After the participant’s eligibility has been confirmed and informed consent has been received, the participant will be randomized into the trial. A form will be provided to investigators and will be used to collate the necessary information prior to randomization. Only when all eligibility criteria and baseline data items have been provided a trial number will be allocated. Participants will be randomized at the level of the individual in a 1:1 ratio to either the experimental group or the control group. The interventions will be implemented based on randomization by investigators.

## Assignment of interventions: blinding

### Who will be blinded {17a}

This study is a non-double-blind trial.

### Procedure for unblinding if needed {17b}

The design is open label, so unblinding will not occur.

## Data collection and management

### Plans for assessment and collection of outcomes {18a}

A predeveloped questionnaire will be completed with patients’ socio-demographic characteristics and required baseline clinical information.

The rest of the information required for the experiment will be collected and assessed as follows:Evaluation of plasma voriconazole trough concentration measurement: the measurement will be carried out half an hour before the second, third, fifth, seventh, and fifteenth doses, once a week after the fifteenth dose, and every 2 weeks after week 4Evaluation of laboratory examination (including the following: blood routine test, CRP, PCT, ESR, FER, LDH, 1,3-β-d-Glucan test (G test), galactomannan test (GM test), hepatic and renal function, coagulation function, arterial blood gas analysis, and blood ammonia): weeks 1, 2, 3, 4, 6, and 8 after the start of the studyEvaluation of imaging tests (including chest CT): once every 2 weeksEvaluation of Child–Pugh score and model for end-stage liver disease (MELD) scores: weeks 1, 2, 3, 4, 6, and 8 after the start of the study

Schedule of assessments is detailed in Table 1.

### Plans to promote participant retention and complete follow-up {18b}

The purpose and importance of the trial will be explained through the research team and PICF during participant recruitment. Participants have the right to withdraw from the trial at any time and for any reason without compromising their medical care and routine treatment by the treatment team or institution. If a participant withdraws from the trial before the end of the study and because the data will be recorded anonymously, an intention-to-treat analysis will be performed on the data for such patients. If a patient withdraws consent during the conduct of the trial and does not wish to consent to the use of data already collected, and if these particular data are retrievable, the investigator will delete the data accordingly.

### Data management {19}

Data will be collected through a paper-based questionnaire, and the collected information will remain anonymous. All data recorded on paper forms will be safely stored in the Department of Infectious Diseases, The Third Affiliated Hospital of Sun Yat-Sen University, Guangzhou, China, following data protection procedures. Data will be entered using a fixed dual researcher and manually reviewed to avoid data entry errors. Data will be saved in Microsoft Excel spreadsheets and stored on the Department of Infection data system of the Third Affiliated Hospital of Sun Yat-sen University.

### Confidentiality {27}

Participants will be assigned a subject’s number for de-identification purposes and all the collected data tables will be identified by the subject’s number only. All data in this study will be stored in a special filing cabinet in the Third Affiliated Hospital of Sun Yat-Sen University. At the same time, we will set access to the file to ensure the security and confidentiality of the data. Only researchers from the Third Affiliated Hospital of Sun Yat-Sen University who participate in this research will have the authorization to access these stored documents.

### Plans for collection, laboratory evaluation, and storage of biological specimens for genetic or molecular analysis in this trial/future use {33}

The collected samples will be sent to the Laboratory of the Third Affiliated Hospital of Sun Yat-sen University for analysis in the first instance, after which they will be discarded instead of being preserved.

## Statistical methods

### Statistical methods for primary and secondary outcomes {20a}

In this study, a separate statistical analysis plan will be developed to analyze the data of the treatment group and the control group. The analyses will be based on Consolidated Standards of Reporting Trials guidelines, and all analyses will be on the principle of intention-to-treat, that is, all participants will be analyzed even if some subjects will fail to follow the original plan during the study. This analysis method can better evaluate the effect of the intervention, reduce bias, and be closer to the actual clinical situation. Our researchers are responsible for the follow-up to ensure that relatively complete data are obtained. Subjects who lacked data on the main results will be excluded in the study from the beginning, including missing CYP2C19 gene, lung CT, abdominal ultrasound, G/GM test, Child–Pugh score, and MELD score.

The PASW18.0 statistical software will be used to analyze the data. The counting data will be expressed by rate, and the rate will be compared by the chi-square test. Continuous normal distribution data will be expressed as mean ± standard deviation, *t*-test will be used for comparison between the two groups, non-normal data will be expressed as median (quartile spacing), Mann–Whitney test method will be used for comparison between the two groups, and *χ*^2^ test will be used for counting data. *P* < 0.05 indicates that the difference is statistically significant. The GraphPadPrism5 software will be to draw.

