## Introduction

### Background and rationale {6a}

Acute-on-chronic liver failure (ACLF) is a prevalent kind of liver failure in which patients acquire acute or subacute liver failure as a result of chronic liver disease [1]. Meanwhile, patients with acute-on-chronic liver failure are more susceptible to fungal infections, particularly the rising incidence of invasive pulmonary aspergillosis (IPA), which has been reported to be as high as 5.0–8.3% [2–4], with a significant increase in short-term mortality (73.5–100%) [2, 3, 5].

At present, amphotericin B, voriconazole, and echinocandins are three frequently prescribed drugs for IPA patients. Voriconazole is recommended as the first-line antifungal agent in the treatment of invasive aspergillosis in the guidelines of the Infectious Diseases Society of America in 2016 [6]. The routine intravenous dosing regimen for voriconazole is as follows: 6 mg per kilogram intravenously twice daily on day 1, then 4 mg per kilogram intravenously twice daily for at least 7 days, after which the patient may switch to oral voriconazole at 200 mg twice daily. The loading dose can make plasma trough concentration (*C*_min_) reach the steady-state concentration of voriconazole in the shortest time (24 h), and the final half-life of voriconazole is only 6 h, so it needs to be administered twice a day [7]. Its therapeutic effect and adverse reactions (such as hepatotoxicity, hallucination, mental abnormality, etc.) are closely related to plasma voriconazole trough concentration. Since voriconazole is mainly metabolized by the liver drug enzyme CYP450, liver injury caused by liver cirrhosis and liver failure may decrease the activity or number of metabolic enzymes, resulting in a decrease in voriconazole metabolism and a corresponding increase in the incidence of adverse reactions [7–10]. Voriconazole drug instructions indicate that for patients with mild to moderate liver cirrhosis (Child–Pugh A and B), the loading dose remains unchanged and the maintenance dose is halved. However, there is no recommendation for patients with severe liver cirrhosis (Child–Pugh C) and liver failure.

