### Outcomes {12}

#### Primary outcome

The primary endpoint will be the antifungal efficacy of voriconazole. All patients treated with voriconazole were systematically evaluated by the same investigator on the team. Each patient was evaluated on the basis of case report, imaging (computed tomography scan, CT) findings. CT images of the lung were reviewed by two radiologists. Changes in lesions were assessed visually using computed planimetry to help estimate percentage change. The response categories for complete response, partial response, and treatment failure were the same as those in similar previous studies [16–19]. Complete responses were defined by the resolution of all clinical signs and symptoms and more than 90% of the lesions due to invasive aspergillosis that were visible on radiology. Partial responses were defined by clinical improvement and greater than 50% improvement in findings on radiology. Stable responses were defined by the absence of change from base line or an improvement of less than 50%. Failure of therapy encompassed progression and death due to IPA. Complete and partial responses were classified as successful outcomes.

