### Methods in analysis to handle protocol non-adherence and any statistical methods to handle missing data {20c}

No imputation of missing data will be performed for statistical analysis.

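### Deaths not due to IPA have no category in the primary outcome and nothing is imputed, so randomised patients can drop out of an analysis described as intention-to-treat; the exclusion sentence in {20a} also needs reconciling with that claim

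*Protocol article*

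**What the plan says.** All references are to the protocol article.

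- **Analysis set, {20a}.** Analyses follow intention-to-treat, explained as "all participants will be analyzed even if some subjects will fail to follow the original plan during the study". The same paragraph then states "Subjects who lacked data on the main results will be excluded in the study from the beginning". Six items are named as examples: two imaging tests (lung CT and abdominal ultrasound), the CYP2C19 genotype, the G/GM test and the two liver scores (Child–Pugh and MELD).
- **Withdrawals, {18b}.** If a participant leaves early, "an intention-to-treat analysis will be performed on the data for such patients".
- **Missing data, {20c}.** "No imputation of missing data will be performed for statistical analysis".
- **Primary outcome, {12}.** Response is complete, partial, stable or failure, and complete plus partial is success. On failure the text says "Failure of therapy encompassed progression and death due to IPA". Death from another cause, and a patient without a follow-up CT, are given no category. No time point is fixed for the response assessment.
- **CT schedule, Table 1.** Lung CT is done at baseline and at weeks 2, 4, 6 and 8.
- **Expected mortality, {6a}.** The background cites short-term mortality of 73.5–100% in these patients, from the literature and without stating the time horizon.

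**The concern.** There are two linked problems. First, the exclusion sentence names lung CT, which determines the primary outcome. Read plainly, it removes randomised patients whose outcome is missing, and that contradicts the promise to analyse everyone.

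Second, even if that sentence concerns baseline data only, the endpoint definition and the bar on imputation together leave some deaths without a value. These patients have liver failure with a bleeding tendency, so death from causes other than IPA is foreseeable.

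At stake is the validity of the primary comparison. Losing deaths after randomisation conditions the analysis on something the regimens may affect. The trial's premise is that the control regimen produces excessive drug levels and toxicity in this population, so the losses need not be equal. The trial is open label ({17b}) and one investigator evaluates all patients (Primary outcome), so a judgement about cause of death can decide who is counted.

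**Working it through.** **1. Does the exclusion sentence contradict intention-to-treat?** Table 1 shows when each listed item is measured.

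| Item | Baseline | Later |
|---|---|---|
| CYP2C19 | yes | none |
| Lung CT | yes | weeks 2, 4, 6, 8 |
| Abdominal ultrasound | yes | weeks 4, 8 |
| G/GM test, Child–Pugh, MELD | yes | weeks 1, 2, 3, 4, 6, 8 |

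- *Outcome reading.* The sentence speaks of main results, and five of the six items recur after baseline. On this reading it contradicts the intention-to-treat claim. Anyone dying before week 4 would lack a follow-up ultrasound and could be excluded.
- *Baseline reading.* All six items are collected at baseline, CYP2C19 only there. The exclusion applies from the start, and {16c} already requires complete baseline items before a trial number is given. On this reading there is no contradiction.

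The wording does not settle which is meant.

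**2. Trace one patient under the baseline reading.** The patient is randomised with complete baseline data and dies of a cause other than IPA before week 2. There is no follow-up CT, so the radiological criteria for complete, partial or stable response cannot be assessed. Unless IPA was judged to have progressed, the definition of failure is not met either. Section {20c} allows no imputed value. The patient therefore has no entry for the chi-square comparison of rates.

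**3. Size of the possible loss.** Inputs are 48 per arm ({14}), mortality m = 73.5–100% ({6a}), and q, the share of deaths not due to IPA. The protocol does not give q, so 25%, 50% and 75% are assumed. Loss per arm = 48 × m × q. Deaths per arm are 48 × 0.735 = 35.3, or 48 at 100%.

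| q | Lost, m = 73.5% | Left of 48 | Lost, m = 100% | Left of 48 |
|---|---|---|---|---|
| 25% | 8.8 | 39.2 | 12 | 36 |
| 50% | 17.6 | 30.4 | 24 | 24 |
| 75% | 26.5 | 21.5 | 36 | 12 |

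These are upper bounds for each q, because a non-IPA death after week 2 may already have a CT-based response.

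**4. Against the dropout allowance.** The plan's step reproduces: 43 / (1 − 0.10) = 47.8, rounded up to 48. If all non-IPA deaths were lost, a 10% loss is reached at q = 0.10 / 0.735 = 13.6%, or q = 10% at 100% mortality. The comparison is only indicative, since the sample size was built on trough concentration above 5 mg/L at day 3, not on response.

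**5. Direction of bias.** If a proportion s of all randomised patients succeed and a proportion u are lost, the observed rate is s / (1 − u). Take s = 20% in both arms (assumed):

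| u, control | u, experimental | Observed, control | Observed, experimental | Spurious difference |
|---|---|---|---|---|
| 30% | 30% | 28.6% | 28.6% | 0 |
| 45% | 30% | 0.20/0.55 = 36.4% | 0.20/0.70 = 28.6% | 7.8 points, favours control |
| 20% | 40% | 0.20/0.80 = 25.0% | 0.20/0.60 = 33.3% | 8.3 points, favours experimental |

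The arm with more lost deaths looks better. The rows are illustrations, not predictions.

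**The case against.** The strongest case against the point runs as follows.

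- *The exclusion sentence is a baseline rule.* This is a fair reading, and the listed items and {16c} support it. It removes the direct contradiction if the authors confirm it. It does not close the gap in the outcome definition.
- *Nothing says non-IPA deaths are removed.* This is true. Under the intention-to-treat statement, a patient without complete or partial response could simply be a non-success, and the separate analysis plan may say so. But the protocol itself lists the response categories and the kind of death that is failure, and it bars imputation. As written, it leaves two defensible denominators for an open-label team to choose between.
- *The loss is exaggerated.* This stands in part. CTs at weeks 2, 4 and 6 could classify later deaths, the mortality range has no stated horizon, and the non-IPA share is unknown. The counts are therefore upper bounds under assumptions.
- *Counting all deaths as failure moves the endpoint from antifungal efficacy towards survival.* This is a real cost. It is why IPA-attributed death should be reported separately.

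A reader might go further and infer that the primary analysis becomes one of survivors with a CT. The documents do not support that. Death due to IPA is classed as failure and needs no CT, so it stays in the denominator. At 73.5% mortality with half of deaths due to IPA, the 30.4 patients left per arm would be 12.7 survivors plus 17.6 IPA deaths. An analysis of survivors only would require that no death is attributed to IPA.

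**Conclusion.** The point holds in this form. The intention-to-treat statement and the exclusion sentence in {20a} must be reconciled, because the latter can be read as an outcome-based or a baseline-only rule. On either reading, a patient who dies of a cause other than IPA before the week 2 CT has no defined primary outcome and can leave the comparison. The analysed set would then be patients with a follow-up CT plus deaths the open-label team attributes to IPA.

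At 73.5% mortality, up to about 9, 18 or 26 of 48 per arm could be lost for assumed non-IPA shares of 25%, 50% or 75%. The actual number cannot be fixed from the protocol. The direction of bias is certain once the arms differ in such deaths, since the arm with more of them gains. Its size is not known, and the differences of about 8 points above rest entirely on assumed figures.

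**What to change.** 1. In {20a}, limit the exclusion to baseline items missing before randomisation, and state that every randomised patient is in the primary denominator.
2. In the primary outcome, name one fixed assessment time from the existing CT schedule. Count death from any cause before that time, or no evaluable response at it, as non-success. Report IPA-attributed death separately.
3. In {20c}, replace the blanket bar with this rule for the primary analysis. Add sensitivity analyses: multiple imputation or a tipping-point analysis for missing response, and one by cause of death.

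The sensitivity analyses are needed because the trial is declared non-inferiority ({8}): counting missing response as failure in both arms can pull the rates together and so favour that conclusion.

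The cost is wording plus a little more analysis work; mortality at weeks 4 and 8 is already recorded. Reported success rates will fall in both arms. If the cited mortality applied before the assessment time, success could be at most 1 − 0.735 = 26.5%, about 12.7 of 48 per arm, and zero at 100% mortality.

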### Methods for additional analyses (e.g., subgroup analyses) {20b}

No additional analyses are planned.

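### Valid but unadjusted two-group tests after simple randomisation of 96 patients give up precision that baseline laboratory values, MELD and CYP2C19, all already collected, could supply

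*Protocol article*

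**What the plan says.** All places are in the protocol article.

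- **Tests** (Statistical methods for primary and secondary outcomes {20a}): for binary data "the rate will be compared by the chi-square test". Normally distributed data get a t-test, and for the rest the "Mann–Whitney test method will be used for comparison between the two groups". No covariate is named for any of them.
- **Further analyses** ({20b}): "No additional analyses are planned".
- **Allocation** (Sequence generation {16a}): "the randomization adopts a simple randomization method". Implementation {16c} adds: "Participants will be randomized at the level of the individual in a 1:1 ratio". No stratification, blocking or minimisation is described.
- **Baseline data** (Table 1): CYP2C19 genotype, MELD, Child–Pugh class and inflammation indicators are all ticked at the baseline visit. Section {20a} goes further and excludes patients who lack certain items, "including missing CYP2C19 gene, lung CT, abdominal ultrasound, G/GM test", Child–Pugh and MELD among them. CYP2C19 and MELD would therefore be complete in the analysed set.
- **SAP** ({20a}): "a separate statistical analysis plan will be developed". It is not shown.

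**The concern.** Neither the design nor the analysis makes use of baseline prognosis. The protocol's own rationale says that it matters. The Introduction argues that liver injury can reduce voriconazole metabolism, and that efficacy and adverse reactions track the trough concentration. The Discussion cites lower clearance in Child–Pugh C cirrhosis or liver failure. Severity of liver disease is therefore a plausible driver of trough, toxicity and outcome.

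Two things are at stake. The first is precision, in a trial of only 96 patients. The second is interpretation: if the arms differ by chance in MELD or genotype, no planned analysis allows for it. The trial is open label, so covariates chosen after the data have been seen would carry little weight. They need to be fixed beforehand.

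**Working it through.** **Starting precision.** Sample size {14} gives rates of 0.6 and 0.3, Z values of 1.96 and 1.28, and 42.16 per arm. Its formula with those inputs gives

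(1.96 × √(0.45 × 0.55 × 2) + 1.28 × √(0.24 + 0.21))² / 0.3² = (1.379 + 0.859)² / 0.09 = 55.6.

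So the stated figure does not reproduce. That is a separate point. It matters here because 48 per arm gives about 85% power for 0.6 v 0.3, not 90%, so there is no precision to spare. The formula also concerns the proportion with trough above 5 mg/L, not the primary response.

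**Chance imbalance, N = 96.**

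- Binary factor with assumed prevalence 50%: SD of the between-arm difference = √(0.25 × 4/96) = 0.102, so P(difference of 10 points or more) = 0.33. Simulation with random arm sizes gives 0.34.
- Assumed prevalence 30%: √(0.21 × 4/96) = 0.094, giving 0.29.
- Continuous factor: SE of the standardised difference = √(2/48) = 0.204. P(above 0.25) = 0.22 and P(above 0.4) = 0.05.

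These probabilities are per factor and describe ordinary randomisation. The effect on an outcome depends on how prognostic the factor is.

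**Laboratory outcomes (CRP, PCT, ESR).** ANCOVA multiplies the variance of the unadjusted follow-up comparison by 1 − ρ², where ρ is the correlation between baseline and follow-up. The documents give no ρ, so a range is assumed.

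| ρ | variance left | cut | 96 patients worth | 80% power becomes |
|---|---|---|---|---|
| 0.3 | 0.91 | 9% | 96/0.91 = 105 | 84% |
| 0.5 | 0.75 | 25% | 96/0.75 = 128 | 90% |
| 0.7 | 0.51 | 49% | 96/0.51 = 188 | 98% |

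The equivalent gain in patients, 1/(1 − ρ²) − 1, is 10%, 33% and 96%.

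**Binary outcome.** No response rates are given, so the 0.6 and 0.3 of the sample-size section stand in. The check simulated 96 simply randomised patients with one normal covariate, 6,000 runs per scenario. It compared the unadjusted chi-square (pooled z) test with a covariate-standardised risk difference from logistic regression.

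| assumed log-OR per SD | variance ratio, adjusted/unadjusted | power, unadjusted to adjusted |
|---|---|---|
| 0 | 1.01 | 85% to 85% |
| 0.5 | 0.96 | 85% to 86% |
| 1.0 | 0.86 | 86% to 91% |
| 1.5 | 0.74 | 86% to 94% |

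With equal rates in both arms (0.6), the rejection rate was about 5% to 6% with either method.

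**The case against.** **This is SAP detail.** A separate SAP is announced, and covariate choice is commonly left to it. The heading of {20b} gives subgroup analyses as its example, so that section need not be read as forbidding an adjusted main analysis. This stands in part: the unseen SAP could still add adjustment. But the protocol is not silent. It names the tests and says that nothing more is planned, so what it does fix is the less efficient choice.

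**The tests are not wrong.** This stands. A reader might infer that unadjusted tests are biased here, or that they cannot tell chance imbalance from a regimen effect. The documents do not support that. Randomisation makes the tests valid, their standard error already allows for chance imbalance, and the simulated type I error is near nominal. There is also no stratification factor that the analysis wrongly omits.

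**The large gains are not for the primary outcome.** This stands too. The 33% and 96% figures belong to secondary laboratory measures. For response, a weak covariate buys almost nothing, and nothing in the protocol quantifies how strongly MELD or CYP2C19 relates to response.

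**Adjustment is not always feasible.** This limits the remedy:

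- The Introduction cites short-term mortality of 73.5–100%. That would leave between 0 and about 25 survivors (0.265 × 96 = 25.4), too few for a safe adjusted logistic model at the upper end.
- Later troughs are affected by death, discontinuation and the trough-driven dose reduction in {11b}, so a model across all ten trough visits would be hard to interpret.
- Trough above 5 mg/L is the basis of the sample size, not a listed outcome.

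**Conclusion.** The point holds as one of efficiency and prespecification, not of validity. The protocol fixes unadjusted comparisons although useful baseline data will be in hand.

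For CRP, PCT and ESR the loss is 9% to 49% of the variance over assumed correlations of 0.3 to 0.7. For the primary response it ranges from nil to about a quarter of the variance (ratio 0.74), and the upper end needs an assumed log-OR of 1.5 per SD. That range also rests on borrowed trough rates. It would be tempting to conclude that the primary comparison is materially underpowered for want of adjustment; the documents give no prognostic strength from which that could follow.

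The change is worth making because it costs little, but a result from the stated tests would still be sound.

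**What to change.** Amend {20a} and {20b}, and carry the following into the SAP before any outcome data are examined:

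- **CRP, PCT, ESR:** ANCOVA of the (log) follow-up value on arm and the (log) baseline value, in place of the t-test or Mann–Whitney test.
- **Primary response:** a covariate-standardised risk difference with 95% CI, from a logistic model with arm and baseline MELD. Keep the chi-square test as a sensitivity analysis. An interval also suits the non-inferiority design declared in {8} better than a P value alone.
- **Trough concentration:** compare log trough at early scheduled visits named in advance, before trough-driven dose changes, adjusted for CYP2C19 group. Trough has no baseline value, so baseline ANCOVA does not apply.
- **Mortality:** adjust only if the numbers of deaths and survivors support the model, by a rule set in advance; otherwise report it unadjusted.

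The covariate set must stay small and fixed, one or two terms per model at this sample size. The cost is wording and a little more programming. No new data are needed.

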**Methods:**

This study is a non-double-blind randomized controlled trial. The 96 eligible acute-on-chronic liver failure patients complicated with invasive pulmonary aspergillosis will be randomly assigned to receive either the optimized voriconazole regimen or the recommended voriconazole regimen for patients with mild to moderate liver cirrhosis (Child–Pugh A and B), at a 1:1 ratio, with an 8-week follow-up period. The antifungal efficacy of voriconazole will be the primary outcome measure. Plasma voriconazole trough concentration, the laboratory examination (CRP, PCT, ESR, etc.), chest CT, adverse events, and mortality at week 4 and 8 will be the secondary outcome measures.

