#### Secondary outcomes

The secondary endpoints will include the following. Half an hour before drug administration, voriconazole plasma concentrations, and laboratory tests of participant were recorded; laboratory tests including C-reactive protein (CRP), procalcitonin (PCT), and erythrocyte sedimentation rate (ESR), etc. Meanwhile, adverse events and mortality at weeks 4 and 8 will also be recorded.

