### Sample size {14}

We referred to a study about drug monitoring and safety of voriconazole therapy in patients with Child–Pugh B and C cirrhosis; this study suggested that about 30% of patients in group B (loading dose, 200 mg intravenously twice daily on day 1; maintenance dose: 100 mg intravenously twice daily) had voriconazole *C*_min_ > 5 mg/L on the third day of treatment [20].

Based on pharmacokinetic knowledge, we estimate that the rate of patients in the experimental group in this study with *C*_min_ > 5 mg/L after 3 days of treatment with voriconazole will not be lower than that in group B described above. The resulting sample size was calculated as follows:$${N}_{c}={\left({Z}_{1-\alpha /2}\sqrt{\overline{P }\left(1-\overline{P }\right)\left(1+r\right)/r} +{Z}_{1-\upbeta }\sqrt{{P}_{c}\left(1-{P}_{c}\right)+{P}_{T}\left(1-{P}_{\mathrm{T}}\right)/r}\right)}^{2}/{\left({P}_{c}-{P}_{T}\right)}^{2}$$

NC: control group sample size.

PC (control group rate): 0.6, PT (experimental group rate): 0.3,

$$\overline{P }$$ (mean of control group rate and experimental group rate): 0.45.

*r*: grouping ratio, *r* = 1 for 1:1 grouping.

*α*: type I error; *β*: type II error.

Here $$\alpha =0.05, \beta =0.1, Z1-\frac{\alpha }{2}=1.96, Z1-\beta =1.28$$

Substituting into the formula: NC ≈ 42.16. By grouping 1:1, then at least 43 cases were taken from each group. Considering 10% dropout, the study will require recruiting approximately 96 participants for all the groups (*n* = 48 in each group) to adequately test the assumption.

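### Mortality at weeks 4 and 8 is compared only as proportions by chi-square; one log-rank test would use the time of death and, under proportional hazards, gain about 4 points of power at 73.5% mortality and about 17 at 95%

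*Protocol article*

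**What the plan says.** Under Secondary outcomes, the protocol article states that "adverse events and mortality at weeks 4 and 8 will also be recorded". Follow-up is fixed: the abstract gives randomisation "at a 1:1 ratio, with an 8-week follow-up period".

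Section {20a} names one test for binary data: "the rate will be compared by the chi-square test". Continuous data are given to the t-test or Mann–Whitney test. No log-rank, Kaplan-Meier or Cox analysis appears. The section announces a separate statistical analysis plan, but section {20b} says that nothing further is planned.

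On incomplete data, section {20c} says: "No imputation of missing data will be performed for statistical analysis". Sections {18b} and {20a} nevertheless promise intention-to-treat analysis, including for patients who withdraw.

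The only mortality level given is in Background and rationale {6a}, which describes ACLF patients with IPA "with a significant increase in short-term mortality (73.5–100" per cent. It comes from cited studies and carries no time horizon.

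**The concern.** Read as written, {20a} has mortality tested as two proportions, one at each time point. Three things follow.

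- **Timing is discarded.** A death on day 3 and a death on day 50 count the same at week 8. If most patients in both arms have died by then, much of the information on a treatment difference lies in when they died.
- **Unknown status has no place.** A proportion at week 8 cannot use a patient whose status at week 8 is unknown, although that patient was known to be alive for part of the period. Imputation is ruled out and no other rule is given.
- **Two overlapping tests.** Each is read at P < 0.05, and the week-8 deaths include the week-4 deaths.

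At stake is the sensitivity of a secondary outcome in a small trial. The primary outcome is not affected.

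**Working it through.** **Inputs from the protocol article.** 48 per arm: Sample size {14} says that "the study will require recruiting approximately 96 participants for all the groups", split equally. Dropout: "Considering 10% dropout". Two-sided 0.05, critical value 1.96. Follow-up 8 weeks.

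**The plan's own figure.** There is no power or event figure for mortality to reproduce. The sample size rests on the proportion with trough concentration above 5 mg/L (0.6 v 0.3). Its step from 43 to 48 per arm reproduces (43/0.9 = 47.8). The 42.16 before it does not follow from the stated β of 0.1: the printed formula gives 55.6. That is a separate matter, and only the 48 per arm is used here.

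**Assumptions, not in the documents.** Hazard ratio 0.6, exponential survival, and control week-8 mortality m₀ of 50%, 73.5%, 85%, 95% and 98%.

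**Formulas.**

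- Experimental arm at week 8: m₁ = 1 − (1 − m₀)^0.6. Control arm at week 4: 1 − √(1 − m₀).
- Log-rank: deaths d = 48(m₀ + m₁); power = Φ(|ln 0.6|·√d/2 − 1.96), with |ln 0.6| = 0.511.
- Chi-square: power = Φ{[(m₀ − m₁)√48 − 1.96√(2m̄(1 − m̄))] / √(m₀(1 − m₀) + m₁(1 − m₁))}, where m̄ is the mean of m₀ and m₁.

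**At 73.5%.** m₁ = 1 − 0.265^0.6 = 0.549.

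- Log-rank: d = 48 × 1.284 = 61.6; Φ(0.511 × 7.85/2 − 1.96) = Φ(0.05) = 0.52.
- Week-8 chi-square: (0.186 × 6.93 − 1.96 × 0.678)/0.665 = −0.06, so 0.475.

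**At 95%.** m₁ = 1 − 0.05^0.6 = 0.834.

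- Log-rank: d = 48 × 1.784 = 85.6; Φ(0.511 × 9.25/2 − 1.96) = Φ(0.40) = 0.66.
- Week-8 chi-square: (0.116 × 6.93 − 1.96 × 0.439)/0.431 = −0.13, so 0.45. The normal approximation runs a little low this near the boundary; simulation gives 0.49.

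**Simulated power** (8-week censoring, no loss to follow-up; repeat runs agree to within about 2 points):

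| Control mortality, week 8 | Experimental, week 8 | Control, week 4 | Chi-square, week 4 | Chi-square, week 8 | Log-rank | Log-rank minus week 8 |
|---|---|---|---|---|---|---|
| 50% | 34% | 29% | 0.22 | 0.35 | 0.36 | about 0 |
| 73.5% | 55% | 49% | 0.36 | 0.48 | 0.52 | 4 points |
| 85% | 68% | 61% | 0.43 | 0.52 | 0.60 | 8 points |
| 95% | 83% | 78% | 0.51 | 0.49 | 0.66 | 17 points |
| 98% | 90% | 86% | 0.51 | 0.38 | 0.67 | 29 points |

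With no treatment effect, the log-rank test rejects in about 5% of trials.

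**With 10% random loss**, dropping from each chi-square anyone lost before the time point, week-8 chi-square v log-rank is 0.45 v 0.50 at 73.5%, 0.48 v 0.57 at 85% and 0.45 v 0.63 at 95%.

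**Front-loaded deaths** (Weibull shape 0.6, hazards still proportional): 0.47 v 0.51 at 73.5% and 0.49 v 0.65 at 95%.

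**Two tests.** If either chi-square is read as positive, the type I error is 9–10% at 73.5–95% mortality. Power is then 57%, 62% and 68% at 73.5%, 85% and 95%, against 53%, 59% and 66% for log-rank in the same runs. With a Bonferroni correction it falls to 47%, 52% and 54%.

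**Non-proportional hazards, 73.5% mortality.** With an effect only after week 4 (hazard ratio 0.4), the week-8 chi-square has 27% and log-rank 15%. With an effect only before week 4 (hazard ratio 0.5), the week-4 chi-square has 54% and log-rank 35%.

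**The case against.** The strongest reply is that nothing here is wrong. Fixed-time mortality over a fixed follow-up is a legitimate endpoint, chi-square is a valid test of it, the outcome is secondary and unpowered, and a statistical analysis plan is announced that may add a survival analysis. Most of this stands and is why the point is only an improvement. It is still fair to raise, because the article does not leave the method open: it names the test for rates and plans no additional analyses.

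Three stronger readings are tempting and are not supported.

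- **That the week-8 comparison must hit a ceiling.** The 73.5–100% is a literature range for short-term mortality without a horizon. Between 73.5% and 95%, week-8 chi-square power is flat at about 0.5. It falls only near the top of the range, and there the week-4 test still has about 0.5.
- **That withdrawn patients are dropped.** This can be inferred from the no-imputation rule, but {18b} and {20a} promise intention-to-treat analysis of everyone. Section {11b} allows voriconazole to be replaced without leaving the trial, and stopping the drug does not make vital status unknown. The text is in tension, not clear.
- **That log-rank always has more power.** The late-effect and early-effect cases show that the ranking can reverse.

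The reply also rightly notes that censoring does not cure withdrawal bias. The dropout criteria name liver and central nervous system toxicity, so censoring may be informative. And the article promises mortality at two time points, not dates of death; with inpatients at recruitment and serious adverse events followed at each visit to week 8, the dates should be obtainable.

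**Conclusion.** The point holds as a modest improvement to a secondary analysis. Under proportional hazards, a hazard ratio of 0.6 and 48 per arm, one log-rank test gains about 4 points of power over the week-8 chi-square at 73.5% control mortality, 8 at 85%, 17 at 95% and nearly 30 at 98%. It exceeds the week-4 chi-square throughout, and at about 50% mortality it equals the week-8 test, so under proportional hazards little is lost if mortality is lower than the background range. It also replaces two overlapping tests with one and gives patients with incomplete follow-up a defined place.

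The hazard ratio and the mortality levels are assumptions; the protocol gives neither for this trial. Even with log-rank, power is only about 0.5 to 0.7 at 73.5% mortality and above, so a non-significant mortality result should not be read as evidence of equal survival.

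**What to change.** Replace the mortality comparison in {20a}, and carry it into the statistical analysis plan, with wording such as:

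> All-cause mortality from randomisation to week 8 will be compared in all randomised patients by the log-rank test, with Kaplan-Meier estimates, their difference and 95% CI reported at weeks 4 and 8. The date of death will be recorded. Vital status to week 8 will be sought for patients who stop voriconazole or leave treatment, where consent allows, and only those whose status remains unknown will be censored at the date last known alive. The number censored will be reported by arm.

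The cost is wording, one date field and a status check for patients who leave treatment. No visits or patients are added. The trade-off is a loss of power under strongly non-proportional hazards, which is why the week-4 and week-8 estimates are kept. Because censoring after toxicity withdrawal may be informative, the counts by arm let a reader judge how far it matters.
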